#### Cardiorespiratory fitness

The 20 m SRT will be used to measure cardiorespiratory fitness [36]. The test involves continuous running between two lines in time to recorded beeps with speed that increases by 0.5 km/hr at each level. It requires minimal equipment and can be administered to a large number of students simultaneously [37]. It is easy to administer and is time efficient, with a maximum test option lasting 22 minutes [37]. Additionally, it is a test that students typically engage with during HPE as part of the curriculum. The 20 m SRT is the most used field test for cardiorespiratory fitness [38]. It has a moderate to high criterion-related validity against peak oxygen uptake (*r*_p_ = 0.62–0.84) in adolescents according to both a relevant meta-analysis [39] and systematic review [38]. The number of laps each participant completes will be recorded. The 20 m SRT will be used as an outcome variable examining differences between groups over time.

#### Muscular fitness

The standing long jump will be used to measure muscular power. This jump involves a two-foot take-off and landing. Students will stand behind a line with both feet and will be encouraged to bend their legs and swing their arms for maximum forward movement. The distance of the jump will be recorded from the line to the back of the student’s foot. Each student will have three attempts. The standing long jump is a practical, time-efficient, and low-cost test [40, 41]. It is valid (*r* = 0.70 with 1 repetition leg extension) and strongly associated with other lower body strength tests (*r* = 0.83–0.86) and upper body strength tests (*r* = 0.69–0.85), making it a general indicator of muscular fitness in youth [40–42]. It is commonly used within the HPE curriculum [25, 43–46]. The standing long jump will be used as an outcome variable examining differences in groups and time.

#### Executive function

An antisaccade task and a visual array task will be conducted on computers using PsychoPy software [47]. These tasks will be used to assess students’ selective attention, inhibition, and working memory and will take approximately 30 minutes to complete [48]. The tasks were pilot tested with Year 8 students and modified appropriately.

The antisaccade task measures inhibitory control of attention and has previously been used in an exercise intervention trial with adolescents [49]. The task will be conducted as previously described [48]. In brief, students will focus on a fixation cross in the centre of their screens. After a visual cue, an asterisk will appear on one side of the screen, followed by a Q or O on the opposite side that is immediately covered by “##”. Students will be told to ignore the asterisk and respond to the Q or O. Due to the classroom setting, the original audio cue for this task was replaced with a visual cue to minimise distraction to other students. Prior to starting the task, students will receive a practice round. They will receive feedback throughout the task on their answers and will be provided with a break in the middle of the 72 responses. This task has good internal consistency (*r* = 0.92) and test-retest reliability (*r* = 0.71) [48]. The number of correctly identified target letters will be used as the outcome variable from the antisaccade task to examine differences between groups over time.

The visual arrays task, which provides a measure of the capacity of working memory and selective attention ability, will also be completed as previously described [48]. Students will see an array of blue and red rectangles flash on screen after being told to focus on one of the two colours. Subsequently, only the colour they were told to remember will appear on screen with one rectangle labelled using a white dot. Students will be asked if that rectangle has changed orientation from the original display. During pilot testing, each array contained five or seven rectangles of each colour. Based on the results and student feedback, an array with three rectangles of each colour was included to ensure an appropriate dosage curve. Before the task begins, students will have two practice rounds. This includes one round with a longer initial flash and one round at full speed. Students will receive feedback throughout the practice, but not during the actual task. The visual arrays task has good internal consistency (*r* = 0.75) and test-retest reliability (*r* = 0.67) [48]. It has previously been used in children as young as 10 years old [50]. The outcome variable of interest from the visual array task is the capacity score *(k)*, which provides a measure of working memory capacity. It is calculated from *N* × (Hits + Correction + Rejections − 1), where *N* is the set-size for that array [48].

#### Motivation

Motivation towards HIIT will be measured using the perceived locus of causality (PLOC) questionnaire that was developed by Goudas et al [51] based on the original questionnaire by Ryan and Connell [52]. It has been used extensively to assess motivation in HPE [53]. The questions are administered using a 7-point Likert scale. For this study, we changed the stem from “I take part in PE/sport” to “I take part in HIIT workouts …” . The questions are based on SDT and assess motivation, external regulation, introjected regulation, identified regulation, and intrinsic regulation to gain an understanding of what motivates students to participate in HIIT [51]. The PLOC will be used as an outcome variable examining differences in groups and time.

#### Basic psychological needs

Three innate psychological needs are encompassed within SDT: autonomy (the need to be self-governed), relatedness (need to feel connected and accepted by others), and competence (the need to succeed in various tasks) [22]. The basic needs theory within SDT hypothesizes that when these needs are met students will have improved intrinsic motivation, wellbeing, and health [22, 54, 55]. Five 7-point Likert scale questions will be used to assess each need. Autonomy during the HIIT workout will be assessed using the questions collated by Standage et al. (2003), who demonstrated internal reliability of the questions in an HPE setting [56]. Relatedness during the HIIT workout will be assessed using a subscale of the Need for Relatedness Scale [57], which has previously been used in HPE with acceptable internal reliability [56, 58]. Lastly, HIIT competence will be assessed using 5 questions from the perceived competence subscale of the intrinsic motivation inventory [59], which has also been shown to be reliable in an HPE setting [56, 60]. The basic psychological needs will be used as an outcome variable examining differences in groups and time.

#### Enjoyment

Enjoyment of general physical activity will be measured for all groups using physical activity enjoyment scale (PACES) before the intervention [61]. The version used in adolescents and youth includes the prompt “When I am active” and 16 phrases that students rank on a 5-point Likert scale from 1 (Disagree a lot) to 5 (Agree a lot) [62]. The overall score is calculated by summing the 16 responses and dividing by the number of questions, with a higher score demonstrating greater enjoyment. It has been validated for both children and adolescents [63]. Enjoyment of general physical activity will be used as a covariate for understanding enjoyment of HIIT specifically.

Enjoyment of HIIT will be also measured using the PACES questionnaire. The stem of the questionnaire will be changed from “When I am active” to “When I am participating in HIIT”. Enjoyment has previously been shown to mediate the effects of school-based physical activity interventions and will be a key variable to examine in this study [64]. The PACES questionnaire on HIIT will be used as an outcome variable examining differences in groups and time.

#### Positive and negative affect

A 9-item questionnaire will be used to assess affect using the prompt “During this workout, I felt”. Students will respond on a 5-point Likert scale from 1 (Not at all) to 5 (Extremely). Five items on the scale are related to positive affect (e.g., proud) and four to negative affect (e.g., unhappy). This is a short-form of the original positive and negative affect scale (PANAS) that was developed to be used in children and has shown to be reliable [65]. This questionnaire will be used as an outcome variable examining differences in groups and time.

#### Self-efficacy

Self-efficacy toward HIIT will be measured using the HIIT-SEQ, which has previously been used with and validated for adolescents [66]. It includes 6 questions on a 10-point Likert scale. It will be an outcome variable used to understand differences in students’ confidence in relation to performing HIIT workouts between groups and over time.

### Intervention measurements

#### Heart rate

Heart rate will be monitored throughout the HIIT sessions and the remainder of the HPE lessons to evaluate intensity for Groups 1 and 2 using Polar H10 monitors (Polar H10, Polar Electro, Finland). Heart rate will also be monitored throughout the HPE lesson in Group 3. Polar H10 monitors will be provided to students and the Polar GoFit system (https://polargofit.com/) will be used to collect data. This will be done anonymously using a number assigned to each student. Students’ maximum heart rates will be determined during the baseline 20 m SRT. Heart rate will be used to assess the fidelity of the HIIT workouts through the calculation of average and peak heart rate, the percentage of students above the thresholds of 80 and 90% of maximum heart rate, and the percentage of time students spend in various deciles (> 80% maximum heart rate, > 90% maximum heart rate).

#### Rating of perceived exertion

The omnibus (OMNI) children’s rating of perceived exertion (RPE) scale will be administered at the end of each HIIT workout for Groups 1 and 2 and at the end of the first and last HIIT workout for Group 3. Students will reflect on how tired they were throughout the entire HIIT session using the prompt “During this workout, I felt”. They will respond using a pictorial scale from 0 (not tired at all) to 10 (very, very tired) [67]. The OMNI-RPE scale has demonstrated strong criterion validity for walking/running against both heart rate and peak oxygen consumption in children aged 11–12 and ≥ 13 years (*r* ≥ 0.82) [68]. A sessional score will be calculated by multiplying the RPE by the duration of the session to represent the load for the entire session. The sessional RPE will be used to assess the fidelity of the HIIT workouts.

#### Enjoyment of HIIT workout

One 5-point Likert scale question will be used to assess students’ enjoyment at the end of each HIIT workout for Groups 1 and 2. Students will rate their enjoyment using the following prompt: “I enjoyed participating in today’s HIIT session” between 1 (strongly disagree) and 5 (strongly agree). A similar style question has previously been used to assess student satisfaction of HIIT workouts [45]. This will be used to understand changes over time in enjoyment and enjoyment of specific workouts and student responsiveness.

#### Process outcomes

The process evaluation will be guided by the Framework for Effective Implementation [20]. The number of schools and students contacted about the study will be tallied to inform the recruitment rate. The number of HIIT workouts delivered by teachers and attended by students will be recorded to inform the dosage delivered and received. Heart rate and RPE will be recorded to assess fidelity to high intensity. Heart rate will also be used to monitor intensity during regular HPE lessons in the control group. Enjoyment of each workout will be recorded to understand student responsiveness. Any adverse events will be recorded by a researcher in a logbook. Any modifications made to the workouts will be recorded by a researcher. Semi-structured interviews will be completed with teachers at the end of phase two on the topic of implementation to investigate adaption and quality.

### Data analysis

Data entry will be completed by one researcher with at least 10% checked by a second researcher. All data will be checked prior to analysis using range to assess any outliers or errors in data entry. To describe the population, descriptive statistics will be reported for each school separately. To determine the effect of the HIIT intervention on cardiorespiratory fitness, muscular fitness, and executive function, general linear models will be used to assess changes in the dependent variables with group (HIIT or control), timepoint, and group x time interaction included as independent variables. To determine the effect of involvement in co-design on students’ motivation, enjoyment, self-efficacy, feelings, and basic psychological needs, generalised linear models will be used to assess changes in the dependent variable, with group (Co-Design or not), timepoint, and group x time interaction included as dependent variables. Potential covariates, such as sex, age, BMI, involvement in co-design, baseline physical activity levels, baseline physical activity enjoyment, and baseline levels of the dependent variable will be identified using two-by-two tests and included in the model where appropriate.

The implementation of *Making a HIIT* will be evaluated using the Framework for Effective Implementation [20] across 8 components: 1) program reach – number of consenting schools and students; 2) dosage – number of HIIT workouts delivered and completed; 3) fidelity – students’ heart rate and RPE during HIIT workouts; 4) quality – variation in heart rate between students; 5) monitoring of control group – via heart rate; 6) responsiveness – student enjoyment and teacher perspectives; 7) adaption – modifications of the HIIT workouts by teachers; 8) differentiation – uniqueness of study.

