### Recruitment and participants

Schools in greater Brisbane will be recruited to *Making a HIIT* through purposeful sampling. Schools with known contacts will be identified and contacted one by one until three schools agree to participate. The aim is to consecutively recruit one co-educational school, one boys’ school, and one girls’ school. The first school will be used as a pilot school to trial the co-design lessons and adapt them if needed before starting in the next two schools. It will include all of the phase one activities and the questionnaires pertaining to students’ motivation, enjoyment, and self-efficacy towards HIIT. The range of included schools aims to help understand potential sex and school-based differences to comprehensively evaluate the integration of co-designing HIIT within HPE.

The head of the HPE department and HPE teachers will be informed of the study and will be involved in class selection for the study. Interested teachers will need to provide informed consent to participate. All students in the classes of consenting teachers will be eligible to participate as *Making a HIIT* will be conducted as part of the curriculum. However, only students who provide parental consent and student assent will have their data collected as part of the study. Students will be excluded if they are unable to participate in the HIIT workouts due to injuries or other reasons. Students will be in either Year 7 or Year 8 (aged 12–14 years) as these 2 years share the same curriculum content descriptions [15]. The flexibility of using Year 7 or 8 allows schools to meaningfully integrate the work conducted as part of the study in their curriculum according to their local needs.

Within each school, *Making a HIIT* will recruit three groups of participants: Group 1) HPE classes involved in the co-design of the HIIT workouts in phase one and who use the HIIT workouts in phase two (Co-Designers); Group 2) HPE classes that use the HIIT workouts in phase two but are not involved in the co-design (HIIT only); and Group 3) HPE classes that continue normal HPE lessons in phase two and are not involved in the co-design (control group). In the pilot school, only one class will be recruited for each group. In the second and third school, two classes will be recruited for each group.

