### Sample size calculation

The sample size calculation was based on the main outcome of phase two, which is cardiorespiratory fitness using the 20-m shuttle run test (20mSRT). An achievable and meaningful difference has previously been reported as between 5 and 6 laps in adolescents for HIIT-based interventions [24, 25]. Six laps will be used in this study. The standard deviation of the 20 m SRT test was 22 laps in a sample of 100 school children aged 13–15 years [24]. Using 3 groups, an α of 0.05, and a power of 80%, we anticipate needing 44 students in each of the three groups based on a G*Power (Version 3.1) calculation (Critical F = 3.066, df = 2) [26]. Based on expected recruitment rates (75–80%), typical class sizes (25–30 students), attrition (5%), and data loss due to absence or abstaining from specific measures (10–15%) [17, 24, 27], two classes will be recruited to each group in schools two and three.

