### Intervention

The intervention will consist of the HIIT workouts designed by Group 1 in phase one. Decisions about the delivery, including the number of HIIT sessions per week and the types of lessons where HIIT is delivered (e.g., theory and/or practical lesson), will be made with teachers, and informed by the local school context. The aim is to have two workouts per week completed in practical and/or theory lessons for a duration of 8 weeks within a single 10-week term. Each HIIT workout will take approximately 10-minutes to complete and will be led by the HPE teacher of each class. For teachers who were not involved in the co-design process, a meeting will be scheduled to discuss the HIIT workouts and expectations for the intervention. All involved teachers will also receive a booklet with the HIIT workout (intervals, exercises with descriptions and modifications, and necessary equipment) for each week. The intervention will be completed by Groups 1 (Co-Designers) and 2 (HIIT only). Following the HIIT workout, HPE lessons will continue as normal. Group 3 (Control) will complete the first and last HIIT workout in the 8-week intervention to be able to appropriately respond to the questionnaires focused on HIIT but will otherwise continue with normal HPE lessons.

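### Intact, teacher-led classes form the groups, but neither the stated model nor the sample size accounts for class

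*Protocol article*

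**What the plan says.** Under Recruitment and participants, each of the three groups consists of HPE classes, and "In the second and third school, two classes will be recruited for each group". The first school is a pilot with one class per group; its listed activities are phase one and the HIIT questionnaires. The Intervention section says that the workouts "will be led by the HPE teacher of each class". The Discussion states that classes are not randomised, because of timetables and class preferences.

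For cardiorespiratory fitness, muscular fitness and executive function, the phase two Data analysis section says "general linear models will be used to assess changes in the dependent variables with group (HIIT or control), timepoint, and group x time interaction" will be used. The questionnaire outcomes get a generalised linear model with the same kind of terms. Candidate covariates are all person-level, and include the baseline value of the outcome. The abstract speaks of linear regressions with covariates.

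The Sample size calculation section takes the shuttle run as the main phase two outcome. It says "Six laps will be used in this study" and "The standard deviation of the 20 m SRT test was 22 laps in a sample of 100 school children aged 13–15 years", and concludes: "Using 3 groups, an α of 0.05, and a power of 80%, we anticipate needing 44 students in each of the three groups". It then allows for recruitment rate, class size, attrition and data loss. It mentions no intraclass correlation and no design effect.

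**The concern.** Group membership is a property of the class, not of the student. Students in one class share a teacher, a timetable, the delivery of the workouts and probably the testing session, so their changes are likely to be correlated. A model without a class term counts students as if each carried independent information about the group effect. The group × time standard error is then too small, and a teacher or class effect can be reported as an effect of HIIT. This bears on the interval and p-value for the main phase two outcome, and the questionnaire models have the same gap. The sample size makes the same assumption, so the stated 80% power does not describe a class-allocated comparison.

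**Working it through.** **1. The plan's own figure.** Inputs from Sample size calculation: 6 laps, SD 22, three groups, α 0.05, 44 per group, critical F 3.066 on 2 numerator df.
- A one-way ANOVA on 3 × 44 = 132 independent students has critical F(2, 129) = 3.066, matching the document.
- With 6/22 = 0.273 entered as the effect size f, the noncentral F power is 79.8%.
- The figure therefore reproduces as a calculation on independent students, with a design effect of 1. Whether 6/22 should serve as f is a separate question, not pursued here.

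**2. Number of classes for the fitness outcomes.** 2 schools × 2 classes × 3 groups = 12. The model compares HIIT with control, so 8 classes against 4.

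**3. Students per class.** From the document's own rates:
- Low end: 25 × 0.75 × 0.95 × 0.85 = 15.1 per class, about 61 per group of four classes.
- High end: 30 × 0.80 × 0.95 × 0.90 = 20.5 per class, about 82 per group.

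I use m = 15 below.

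**4. Error rate if pairing is handled but class is ignored.** The ICC of the change score is assumed. DE = 1 + (m − 1) × ICC, and actual error ≈ 2[1 − Φ(1.96/√DE)].

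| ICC (assumed) | DE | Naive SE ÷ true SE | Actual two-sided error |
|---|---|---|---|
| 0.01 | 1.14 | 0.94 | 6.6% |
| 0.02 | 1.28 | 0.88 | 8.3% |
| 0.05 | 1.70 | 0.77 | 13.3% |
| 0.10 | 2.40 | 0.65 | 20.6% |

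Simulation of 12 classes of 15 (8 against 4, SD 22) agrees: 12.6–13.2% at ICC 0.05 and 20.5–20.8% at 0.10. A t test on class means stays at 4.6–5.0%.

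**5. Power of a valid class-level analysis for 6 laps.** Pre–post correlation r is assumed to be 0.7 or 0.8.
- SD of change = 22 × √(2(1 − r)) = 17.0 or 13.9 laps.
- SE = √[SD² × DE/15 × (1/8 + 1/4)], tested on 10 df (12 classes − 2).
- Best case at ICC 0.05–0.10 (r = 0.8, ICC 0.05): SE = 2.87, 6/2.87 = 2.09, power 47%.
- Worst case (r = 0.7, ICC 0.10): SE = 4.17, 6/4.17 = 1.44, power 26%. Giving one df to school makes it 25%.
- At ICC 0.01–0.02, power is 43–63%. At ICC 0 it is 52–69%.

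**6. How far the planned recruitment absorbs clustering.** Keep the document's own effect size and ask when n/DE falls to 44:
- 61 students in classes of 15.1: (60.6/44 − 1)/14.1 gives ICC 0.027.
- 82 students in classes of 20.5: (82.1/44 − 1)/19.5 gives ICC 0.044.

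**7. If rows really were analysed as independent.** Ignoring the pairing makes the group × time SE too large by 1/√(1 − r), which is 1.8 to 2.2 for r of 0.7–0.8 with no class effect. In simulation at ICC 0.05–0.10, the error rate is then 0–2%. This works in the opposite direction to step 4.

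**The case against.** A reader might infer that the plan treats every row as independent, including the two rows of one student, and so suffers both errors at once. The document does not support this. It never says that rows are independent. Its talk of assessing changes, and its listing of the baseline outcome as a possible covariate, fit a repeated-measures, change-score or baseline-adjusted model at least as well. The two harms also exclude each other: the inflation in step 4 arises only when pairing is handled, and the oversized standard error in step 7 only when it is not. What stands at student level is a request to state the structure.

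It can also be said that the ICC is assumed and may be small, and that recruiting four classes per group gives a margin above 44 students. Both are fair. At ICC 0.01–0.02 the inflation is mild, and the margin covers an ICC up to about 0.03–0.04 on the document's own effect size. But a larger sample does not repair a model that omits class. Nor does it supply the missing degrees of freedom, which depend on 12 classes.

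Finally, an article may leave detail to a fuller plan. Here, however, it names the model family and terms and bases its sample size on independent students. None of the readings of the student level brings class into the model.

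**Conclusion.** The point holds at class level. Allocation and delivery are by class, while the stated model and sample size contain nothing for class. With pairing handled and 15 students per class, the true error rate is about 7–8% at ICC 0.01–0.02 and about 13–21% at 0.05–0.10, against a nominal 5%. The direction follows from the design for any positive ICC. The size rests on assumed ICCs, and the power figures also on an assumed pre–post correlation of 0.7–0.8. At student level the wording is ambiguous rather than shown to be wrong. Because this governs inference on the main phase two outcome, it should be corrected before analysis.

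**What to change.** - **Data analysis, fitness and executive function.** Say that class is accounted for by a method suited to few clusters. Any of these would do: a mixed model with random effects for class and student and small-sample degrees of freedom; a baseline-adjusted post-test model with a class random effect; or an analysis of class means. Include school in the model, and state how each student's two values are linked.
- **Data analysis, questionnaires.** Use the same structure. There are 15 classes if the pilot school's three are included.
- **Sample size calculation.** Replace the 80% claim with power computed using a design effect and class-level degrees of freedom over a stated ICC range.

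**Cost.** No new data are needed, since class and school are known by design. Intervals will be wider than under a model that ignores class. The stated power will be less favourable: about 25–47% for 6 laps with 12 classes of 15, r 0.7–0.8 and ICC 0.05–0.10, and higher at smaller ICC. The sponsor would have to acknowledge that loss or recruit more classes.

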#### Phase two:

Determine the effect of a HIIT intervention on cardiorespiratory fitness, muscular fitness, and executive function.Determine the effect of the co-design process on students’ enjoyment, self-efficacy, affect, basic psychological needs, and motivation towards the HIIT workouts.Evaluate whether the intervention was implemented as intended through a process evaluation using the framework described by *Durlak and DuPres* [20].

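### As written, the co-design comparison pools HIIT Only with Control, so part of any HIIT-programme effect enters the co-design estimate

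*Protocol article*

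**What the plan says.** The second phase two objective in the protocol article begins "Determine the effect of the co-design process on" and goes on to list enjoyment, self-efficacy, affect, basic psychological needs and motivation towards the workouts. The phase two Data analysis section answers it with a model "with group (Co-Design or not), timepoint, and group x time interaction included as dependent variables". (Calling these terms dependent variables is a separate wording slip; they are plainly meant as predictors.)

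Recruitment and participants defines Group 2 as "HPE classes that use the HIIT workouts in phase two but are not involved in the co-design (HIIT only") and Group 3 as "HPE classes that continue normal HPE lessons in phase two and are not involved in the co-design (control group"). Under Intervention, the 8-week programme goes to Groups 1 and 2, with two workouts a week as the aim. The same section says that Control "will complete the first and last HIIT workout in the 8-week intervention to be able to appropriately respond to the questionnaires focused on HIIT". Pre-intervention and post-intervention measurements has these questionnaires completed by all groups after the first and the last workout.

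The fitness and executive function outcomes have their own model, "with group (HIIT or control), timepoint, and group x time interaction included as independent variables". That HIIT-or-control factor is not assigned to the questionnaire outcomes.

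**The concern.** Group 1 differs from Group 2 in co-design. It differs from Group 3 in co-design and also in how much of the HIIT programme it received. A factor coded as co-design or not puts Groups 2 and 3 on the same side, so its coefficient mixes two effects, while the objective asks about one.

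The mixing falls mainly on the group x time term. At the first questionnaire, Groups 2 and 3 have each done one programme workout. By the last, Group 2 has had the whole programme and Group 3 its second workout. If repeated HIIT changes enjoyment, motivation or self-efficacy through habituation, boredom or growing competence, that change is partly credited to co-design or charged against it. Co-design is the component that the protocol's Discussion presents as novel, so a wrong answer here matters.

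**Working it through.** **The plan's own figure.** The Sample size calculation gives 44 per group. Entering 6/22 = 0.273 as the effect size f in a three-group F test with 132 students gives a critical F of 3.066 and power of 0.798, so the figure reproduces to within rounding. It concerns the shuttle run and does not size the co-design comparison, so it neither supports nor weakens this point.

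**Who is in the comparator.**

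| Group | Co-design | Phase two HIIT workouts | Questionnaires |
|---|---|---|---|
| 1 Co-Designers | yes | 2 per week × 8 weeks = about 16 (intended) | yes |
| 2 HIIT Only | no | about 16 (intended) | yes |
| 3 Control | no | 2 (first and last) | yes |

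Nothing restricts the model to Groups 1 and 2, so the comparator is Groups 2 and 3 together.

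**What the contrast estimates.** Let G1, G2 and G3 be the mean changes from first to last questionnaire. With equal groups:

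G1 − (G2 + G3)/2 = (G1 − G2) + 0.5 × (G2 − G3)

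The first term is the co-design contrast with the phase two programme held constant. The second is half the HIIT-exposure effect. With unequal groups, 0.5 becomes Group 3's share of the pooled comparator. This is algebra and needs no outside figure.

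**Covariates.** The named candidates include involvement in co-design. That can help the HIIT-or-control model, but here it duplicates the factor itself. HIIT exposure is not named.

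**Students per group for these outcomes.** The pilot school supplies the questionnaires too, with one class per group; schools two and three supply two each, so there are 1 + 2 + 2 = 5 classes per group. Using the class sizes and rates in the Sample size calculation:

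- Low: 25 × 0.75 × 0.95 × 0.85 = 15.1 per class; × 5 = 76.
- High: 30 × 0.80 × 0.95 × 0.90 = 20.5 per class; × 5 = 103.

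**False rejection if co-design does nothing.** The documents give no HIIT-exposure effect on these scales, so h = 0.3 to 0.5 SD is an assumption. With unit SD of change and no clustering:

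- Bias = 0.5h = 0.15 to 0.25 SD.
- Standard error of the pooled contrast = √(1/n + 1/(2n)) = √(1.5/n), which is 0.140 at n = 76 and 0.121 at n = 103.
- Rejection rate = Φ(z − 1.96) + Φ(−z − 1.96), where z = 0.5h/√(1.5/n).

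| n per group | h | bias (SD) | z | rejection rate |
|---|---|---|---|---|
| 76 | 0.3 | 0.15 | 1.07 | 19% |
| 76 | 0.5 | 0.25 | 1.78 | 43% |
| 103 | 0.3 | 0.15 | 1.24 | 24% |
| 103 | 0.5 | 0.25 | 2.07 | 54% |

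On the same assumptions, Group 1 v Group 2 rejects 5% of the time. At the planned minimum of 44 per group, the pooled contrast rejects 13% (h = 0.3) to 27% (h = 0.5). A larger sample does not reduce the bias; it makes false rejection more likely.

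**Masking.** With a true co-design effect of 0.3 SD and an assumed exposure effect of −0.6 SD, the pooled estimate is 0.3 + 0.5 × (−0.6) = 0.

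**The case against.** The strongest reply is that the article never says in words that Groups 2 and 3 are combined. It gives a short label, the measurement sections speak of differences in groups and time, the covariate list is open-ended, and workouts delivered and attended are recorded. A fuller analysis plan might name the right contrast. What stands is that pooling is an inference from the group definitions and from questionnaire collection in all groups. It is still the natural reading of a two-level label, and nothing shown pre-specifies a HIIT-exposure term or drops Control. The objection is to a factor that the article states, not to detail left for another document.

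Several stronger readings are tempting but unsupported:

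- A reader might take Control to be unexposed, or its last workout to be those students' second HIIT session ever. Control does two programme workouts, and nothing is said about earlier HIIT experience. The contrast is low against high exposure.
- A reader might infer that Group 1 v Group 2 isolates co-design cleanly. Classes are not randomised, and Group 1 tries several HIIT workouts and pilots its own in phase one. That contrast holds the phase two programme constant, but it includes the phase one exposure as part of the co-design package.
- A reader might infer that the HIIT Only group exists for this contrast. The article gives no such rationale.
- A reader might conclude that the result is certain to be biased. If repeated HIIT does not move these scales, the bias is zero.

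The main phase two outcome, the shuttle run, is not affected.

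**Conclusion.** The point holds for the analysis as written: the stated two-level factor does not match the second phase two objective. With equal groups, half of any effect of the 8-week programme on these scales enters the co-design group x time estimate. That fraction follows from the coding alone.

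The size in practice depends on an exposure effect that the documents do not give. The 0.15 to 0.25 SD bias and the 19% to 54% rejection rate are illustrations that rest on an assumed 0.3 to 0.5 SD exposure effect, no co-design effect, equal groups of 76 to 103, unit SD and no allowance for class clustering. The direction is unknown: the pooling could create an apparent co-design effect or hide a real one.

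**What to change.** Replace the two-level factor for the questionnaire outcomes with a three-level group factor, interacted with time. Define the co-design effect as Group 1 v Group 2, and report Group 2 v Group 3 separately as the HIIT-exposure contrast. Separate co-design and HIIT terms, each interacted with time, are equivalent and also use all three groups. State that Group 1 v Group 2 is non-randomised and carries Group 1's phase one HIIT exposure as part of co-design. Correct the description of the group terms as dependent variables in the same edit. If Group 1 v Group 2 was always intended, one sentence saying so is enough.

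The cost is wording and some precision. For the same residual SD and equal groups, the standard error rises from √(1.5/n) to √(2/n), a ratio of √(2/1.5) = 1.15, so the interval is about 15% wider. Data collection does not change.
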